#### The depression anxiety stress scale-21 (DASS-21), Chinese version

2.7.1

The DASS-21 is a concise yet reliable self-report instrument designed to assess the severity of negative emotional states, specifically depression, anxiety, and stress, over a given period (Cao et al., 2023).

The scale comprises 21 items, divided equally into three subscales, with each subscale containing seven items that evaluate symptoms related to depression, anxiety, and stress.

Stress subscale scores range from 0 to 34, with severity levels classified as follows: normal (0–14), mild (15–18), moderate (19–25), severe (26–33), and extremely severe (≥34). The Chinese version of the DASS-21 has been validated and demonstrates strong reliability and validity in assessing psychological distress among Chinese-speaking populations.

#### Quality of life scale for children and adolescents (QLSCA)

2.7.2

The QLSCA is a multidimensional self-report instrument designed to assess the quality of life of primary and secondary school students aged 7 to 18. It evaluates four core domains: physical well-being, psychological well-being, social functioning, and living environment. Specific dimensions include physical health, mental health, social relationships, environmental conditions, and overall life satisfaction.

The QLSCA uses a four- or five-point Likert scale to capture responses, generating both an overall score and subscale scores for each dimension. These scores provide a comprehensive overview of a child’s or adolescent’s perceived quality of life. The Chinese version of the QLSCA has demonstrated strong reliability and validity in previous studies (Wu et al., 2006).

#### Physical fitness performance

2.7.3

The Physical Fitness Test for Chinese Secondary School Students serves as a comprehensive tool to assess students’ overall physical fitness levels (Zhang et al., 2021).

It covers various aspects, including physical form (e.g., height and weight), physical function (e.g., lung capacity), and physical fitness (e.g., 50-meter sprint, seated forward bend, standing long jump, pull-ups/sit-ups, and endurance running). Test results will be converted into individual and total scores based on standardized scales and weightings. Students will then be classified into four performance categories excellent, good, pass, and fail according to their total scores for the academic year.

#### Academic performance

2.7.4

The relationship between academic achievement and mental health is complex, characterized by mutual influence and interdependence. On one hand, academic pressure stemming from performance expectations can negatively affect students’ mental health, potentially leading to emotional issues such as anxiety and depression (Talley, 2024). On the other hand, a strong sense of academic achievement can enhance students’ self-esteem and self-confidence (Cuc and Cuc, 2019).

Moreover, students’ mental health directly influences their learning efficiency, emotional regulation, and overall academic performance (Usán Supervía and Quílez Robres, 2021). Given this bidirectional relationship, we will use the total scores from all subjects in the midterm and final examinations as indicators of academic achievement.

### Interviews

2.8

The purpose of the qualitative phase is to explore participants’ and PE teachers’ perceptions and experiences with the TABATA training module. Based on previous study (Hoover et al., 2018), the interview questions will address various topics, including participation experiences, physical responses, psychological effects, curriculum design, and suggestions for improvement. The interview transcript is shown in Tables 5, 6.

**Table 5 tab5:** The students interview transcript template.

No.	Interview question
1.	Please describe your experience participating in the TABATA training course.
2.	What was the most memorable movement for you throughout the entire module? Why?
3.	During the training, what specific physical changes did you notice? (e.g., fatigue level, heart rate, amount of sweating, muscle sensation)
4.	What impact do you think the TABATA training has had on your physical fitness, endurance, or overall physical condition?
5.	How did you typically feel emotionally after participating in TABATA training? (e.g., excited, stressed, focused, bored).
6.	During or after the training, did you experience any changes in your sense of accomplishment, motivation, self-confidence, or willpower? Please describe specifically.
7.	Were there moments when you felt anxious, apprehensive, or wanted to give up? How did you cope with them?
8.	Do you think the current structure, duration, intensity, and movement arrangement of the TABATA training module are reasonable? Why?
9.	What are your thoughts on the music, the teacher’s demonstrations and explanations, and the monitoring bracelet?
10.	What do you think are the advantages and potential disadvantages of this training method, respectively?
11.	Would you be willing to recommend this course to classmates? Why or why not?
12.	Regarding safety, what areas do you think require special attention or need more guidance?
13.	Do you have any suggestions?

**Table 6 tab6:** The teachers interview transcript template.

No.	Interview question
1.	Please describe what it’s like to lead a TABATA training session.
2.	What burdens do you face while conducting TABATA training?
3.	How would you describe the overall engagement and emotional responses of the students toward the TABATA training?
4.	What impact do you believe this training program will have on students’ physical and mental fitness?
5.	Do you consider the current structure of the TABATA module (duration, intensity, exercise sequence) to be appropriate?
6.	How do you feel about the music used in the course and the monitoring devices? How do these elements impact teaching effectiveness and your workload?
7.	During implementation, which movements do you consider to pose higher security risks?
8.	What specific suggestions do you have for improving this intervention plan?

A semi-structured interview format will be adopted (Ruslin et al., 2022) in this study, allowing for in-depth exploration while maintaining a consistent framework across to facilitate in-depth exploration within a consistent framework. This phase will focus particularly on evaluating the acceptability and feasibility of the TABATA training module. Participants will from the intervention group and the physical education (PE) teachers who delivered it. To capture diverse perspectives, we aim to interview a minimum of 2 PE teacher and at least 20 students, ensuring representation of different roles within the program (Bekele and Ago, 2022). We will also strive to maintain a gender balance among student participants, targeting an approximate 1:1 male to female ratio to account for potential perceptual differences (Smith et al., 2018). This sampling approach is designed to ensure a meaningful variation in experiences and viewpoints.

The determination of data saturation will follow the methodological framework proposed by Francis (Francis et al., 2010). Specifically, data collection will commence with an initial set of 10 interviews. Following this, interviews will be conducted and analyzed in iterative batches of three. This process will continue until a complete batch yields no new themes or substantive information, at which point saturation will be considered achieved. This iterative approach ensures methodological rigor in meeting qualitative saturation standards while optimizing the efficient use of research resources.

Safeguarding the emotional well-being of adolescent participants, who experiencing psychological stress, is a central ethical priority. A protocol will be established for this purpose. First, written informed consent will be obtained from both participants and their guardians, detailing the interview’s purpose, potential risks, confidentiality, and the unconditional right to withdraw. These points will be verbally reaffirmed at the interview’s outset. Second, all interviewers will receive specialized training in engaging with vulnerable youth. They will be instructed to monitor participants for signs of stress throughout the session and to terminate the interview immediately upon such signs or the participant’s explicit request to stop. Finally, each interview will be designed to last approximately 10 min to minimize potential fatigue and anxiety, ensuring focus remains on the core topics.

### Data analysis

2.9

The analysis will focus on obtaining descriptive statistics and confidence intervals for the variables. Participants will be characterized by means, standard deviations, and ranges for quantitative variables, as well as counts and proportions for categorical variables. Since this is a feasibility study primarily aimed at testing our ability to collect data, we will not use data interpolation to address any missing data. Based on the proposal for the pilot study, we have set the following feasibility goals: within 1 month, the intervention group and the control group will each recruit 20 to 30 participants; achieving a recruitment rate of over 70% in the TABATA intervention group; ensuring that more than 80% of students in the TABATA training group complete the 8-week intervention; having more than 70% of adherence rate; and maintaining an overall missing data rate of less than 10%.

All interviews will be recorded using an Apple mobile phone and transcribed verbatim, followed by manual proofreading using Flying Book of Notes software. To gain a comprehensive understanding of participants’ perceptions, an inductive analysis approach will be employed to identify broader themes (Azungah, 2018). Data will be analyzed using NVivo 12 qualitative analysis software to extract key themes related to feasibility and acceptability.

To enhance the credibility and reliability of the findings, researcher triangulation will be used to minimize researcher bias and strengthen the overall robustness of the study (Natow, 2020). First, one member of the research team will input the transcribed data into NVivo 12 and conduct initial coding in collaboration with another team member, merging codes to form preliminary themes. Next, two additional researchers will review the coding and refine the thematic structure for further integration.

Inter-rater reliability will be assessed by calculating the Kappa coefficient using NVivo 12. A Kappa value greater than 0.75 will be considered acceptable, indicating high consistency and data validity. Finally, all members of the research team will convene to finalize the themes related to the feasibility and acceptability of the TABATA training module.

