### Study design

2.1

This is a two-stage, mixed-methods study comprising an initial feasibility randomized controlled trial (RCT), followed by a qualitative study. The reporting of this protocol will adhere to the SPIRIT guidelines. This study will be conducted in secondary schools in Nanjing City, Jiangsu Province, China. The research protocol received its primary ethical review and approval from the Ethics Committee of Nanjing Normal University (Approval Number: NNU202407008; Date: July 2024), which holds the principal oversight responsibility for ensuring full compliance with all applicable Chinese laws and regulations, including specific provisions for the protection of minors. Approval from the Universiti Kebangsaan Malaysia Research Ethics Committee (JEP-2024-544) was obtained subsequently by the project lead (a UKM doctoral candidate) for institutional academic purposes, contingent upon the primary approval from Nanjing Normal University. Consequently, all research activities will be carried out under the supervision and in accordance with the requirements of the Nanjing Normal University Ethics Committee. This study was also approved by Nan Hang Secondary School in October 2023. Upon verbal agreement, informed consent and assent forms will be obtained from parents and children, respectively.

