### Recruitment and randomization

2.4

The participants in this study will be middle school students in Nanjing, Jiangsu Province, who are experiencing psychological stress. During the selection stage, students will complete the Chinese version of the DASS-21 questionnaire on a large scale through their school’s IT classes. Students with stress scores exceeding 19 will be identified as potential participants.

This study will employ a cluster randomized design. After obtaining informed consent, eligible participants will be grouped by their respective schools. All participants from one school will be assigned to the intervention group and receive the uniform intervention during the specified period. All participants from the other school will be assigned to the control group, maintaining their routine learning and daily activities without any intervention. During the evaluation process, outcome assessors will be blinded to ensure they remained unaware of the group assignments. This design is intended to minimize disruptions to regular teaching activities while ensuring participant privacy and safeguarding against potential stigmatization. Additionally, it helps prevent contamination between intervention and control groups, thereby preserving the study’s internal validity.

Given that the participants were minors experiencing psychological stress, strict measures were taken to ensure their privacy. All personal identifiers were removed from the transcribed data, and code numbers were used in place of participant names. Transcription files were encrypted and stored on a password-protected, stand-alone device, while physical materials were secured in a locked filing cabinet accessible only to the research team. All raw data were securely destroyed within 10 years of the study’s completion.

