Participants in the intervention group will undergo 8 weeks of TABATA training, while those in the control group will not receive any intervention or participate in any interviews. Table 1 outlines the participant recruitment timeline, key milestones, and scheduled assessment activities. Stage 2 will involve the qualitative phase of the study. Participants for this phase will be selected from the intervention group in Stage 1. Individual interviews will be conducted with a subset of students who received the intervention, as well as with PE teachers who delivered the training. The aim of this phase is to evaluate the feasibility and acceptability of the TABATA training module.

**Table 1 tab1:** SPIRIT (Standard Protocol Items: Recommendations for Interventional Trials) schedule of enrolment, interventions, and assessment.

Timepoint	Study period										
	Enrolment	Allocation	Post-allocation								Close-out
	9/2025–10/2025	9/2025–10/2025	Week 1	Week 2	Week 3	Week 4	Week 5	Week 6	Week 7	Week 8	12/2025
Enrolment											
Screening	✓										
Eligibility screen	✓										
Informed consent	✓										
Allocation		✓									
Interventions											
Intervention A											
Control											
Assessments											
DASS-21 Chinese version		✓				✓				✓	
Quality of life scale for children and adolescents (QLSCA) Chinese version		✓				✓				✓	
Physical fitness performance		✓				✓				✓	
Blood pressure		✓				✓				✓	

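### Section 2.9 limits the primary recruitment rate to the TABATA group although Table 3 covers all eligible students, and Table 1 does not close consent at both schools before the school assignment

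*Protocol article*

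**What the plan says.** **Order of consent and assignment.** Section 2.4 is the only place that gives an explicit sequence: "After obtaining informed consent, eligible participants will be grouped by their respective schools". It then says "All participants from one school will be assigned to the intervention group and receive the uniform intervention during the specified period" and "All participants from the other school will be assigned to the control group, maintaining their routine learning and daily activities without any intervention". It calls the design cluster randomized. The blinding it describes covers outcome assessors only.

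**Schedule.** Table 1 has separate columns for enrolment and allocation, with enrolment first and informed consent ticked only under enrolment. Both columns carry the same dates: "9/2025–10/2025 9/2025–10/2025".

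**Recruitment rate.** Table 3 lists it among the primary outcomes, with a threshold of more than 70%, and counts all students who are eligible and agree to take part. The Discussion repeats the threshold without restricting it to an arm. Section 2.9, in its list of feasibility targets, names only the TABATA arm for this rate ("within 1 month, the intervention group and the control group will each recruit 20 to 30 participants; achieving a recruitment rate of over 70% in" that arm).

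**The concern.** The recruitment rate has two definitions: all eligible students in Table 3, and the TABATA group alone in section 2.9. It is a primary feasibility measure with a pass mark, so the choice of denominator can decide whether the goal is met.

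The timing adds to this. In an individually randomised trial, obtaining each participant's consent before that participant's allocation is enough. Here a single assignment fixes the arm of every student at both schools. The order in section 2.4 therefore protects the trial only if consent has closed at **both** schools before the assignment is made or disclosed. The shared window in Table 1 does not secure that.

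If the assignment became known early, later families at one school would be consenting to a known training programme, and those at the other to assessments with no programme. A rate taken at the TABATA school alone would then measure willingness to join a known programme. A later randomised trial needs willingness to be allocated. The students who consent could also differ between arms, which would carry over into the stress, quality-of-life and fitness comparisons.

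**Working it through.** The article states no figure to reproduce on this point. The check compares the passages and then illustrates the possible size.

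**1. The passages side by side**

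| Place | Recruitment rate | Order or timing |
|---|---|---|
| Section 2.4 | – | Consent, then grouping and assignment by school |
| Table 1 | – | Enrolment and allocation both 9/2025–10/2025 |
| Table 3 | All eligible students, >70% | – |
| Section 2.9 | TABATA group, >70% | 20 to 30 per group within 1 month |
| Discussion | >70%, no arm named | – |

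The denominators in Table 3 and section 2.9 conflict. The dates in Table 1 are compatible with section 2.4, but they also allow an assignment before the last consent.

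**2. What the threshold means in numbers**

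Section 2.9 aims for 20 to 30 recruits per group. For the rate to exceed 70%, 20, 25 or 30 recruits can come from at most 28, 35 or 42 eligible students (20/28 = 25/35 = 30/42 = 71.4%). The illustrations below use 35 eligible students per school, of whom at least 25 must consent.

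**3. Effect of the denominator (assumed consent rates)**

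Assume 80% consent at the TABATA school and 60% at the control school.
- Section 2.9 wording: 28/35 = 80%, which passes.
- Table 3 wording: (28 + 21)/70 = 49/70 = 70%, which does not exceed 70% and fails.

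**4. Effect of a shift in consent (assumed consent rates)**

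The chance of passing at one school is P(X ≥ 25), with X binomial(35, p):

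| True consent p | 60% | 65% | 70% | 75% | 80% |
|---|---|---|---|---|---|
| Chance of passing | 0.11 | 0.27 | 0.51 | 0.76 | 0.93 |

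If knowing the arm raised consent from 65% to 75%, the chance of passing would rise from 0.27 to 0.76. With 28 eligible students the same shift gives 0.31 to 0.75, and with 42 it gives 0.24 to 0.77.

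**5. Effect on who enters each arm (assumed model)**

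Take a normally distributed propensity to consent that has correlation ρ with the outcome. If a fraction q consents, the mean outcome among consenters shifts by ρ·φ(z)/q SD, where Φ(z) = q.
- At ρ = 0.3, q = 0.75 gives 0.127 and q = 0.60 gives 0.193. The spurious difference between arms is 0.066, or about 0.07 SD.
- Over ρ = 0.2 to 0.5, 75% against 60% gives 0.04 to 0.11 SD.
- A wider gap of 80% against 50% gives 0.13 SD at ρ = 0.3, with a range of 0.09 to 0.22 SD.

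For comparison, the standard error of a between-arm difference, ignoring clustering, is √(2/25) = 0.28 SD at 25 per arm and √(2/30) = 0.26 SD at 30 per arm.

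**The case against.** The strongest reply is that the only explicit statement of sequence puts consent first. A reader might infer from section 2.9 that the arms already exist when recruitment starts, so that families know their arm when they consent. The article does not support this. The phrase about each group recruiting 20 to 30 can be a per-group size target, in line with the per-group sample size in section 2.2. A rate for one group can also be calculated after allocation from that school's counts. Nor do the Table 1 dates prove overlap: they are given by month, and recruitment within 1 month leaves room for allocation in the second. This part of the objection stands, so the finding is a possible bias and not a demonstrated one.

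A reader might also take the sentence "This study was also approved by Nan Hang Secondary School in October 2023" as a sign that this school's arm was settled early. It records an approval and says nothing about an arm, so it carries no weight here.

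Two further points stand. How the draw is generated, who makes it and how the consent form is worded are details that an article may leave to the full protocol. The selection effect in step 5 is also small beside the sampling error, and it touches secondary outcomes that section 2.9 summarises with descriptive statistics and confidence intervals.

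The objection does not remove the conflict between section 2.9 and Table 3. It also leaves the article without any statement that consent closes at both schools before the assignment is made or disclosed.

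**Conclusion.** The concern holds in a limited form. Section 2.9 and Table 3 define a primary outcome over different students, and the stated dates do not secure the section 2.4 order at the level of the school, which is where it matters. Early knowledge of the arm **could** bias the recruitment rate and the make-up of the arms; the article does not show that it will.

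The denominator conflict can reverse the result: under assumed consent of 80% and 60%, the goal is met on one definition (80%) and missed on the other (70%). A ten-point shift in consent around the threshold could move the chance of passing from about 0.27 to 0.76. All consent rates, the 35 eligible students per school and the correlations are assumptions, because the article gives none. The main exposure is the primary recruitment rate; the effect on outcome comparisons is likely to be modest. The changes are worth making before enrolment starts because they affect a primary feasibility criterion and cost little.

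**What to change.** - **Section 2.9:** calculate the recruitment rate over all eligible students at both schools, as Table 3 does, and apply the >70% threshold to that rate. Report each school's rate beside it. State the 20 to 30 target as the number to be enrolled at each school.
- **Table 1:** give enrolment and allocation dates that do not overlap, for example enrolment in 9/2025 and allocation in 10/2025.
- **Section 2.4:** add one sentence saying that enrolment and consent end at both schools before the school assignment is made and disclosed.

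**Cost.** These are changes of wording and dates, with no extra participants or procedures. The recruitment rate may come out lower than a rate from the TABATA school alone. The two 1-hour PE-teacher training sessions, with the practical assessment that follows, must fit between the assignment and Week 1.
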